##### Straining level

The degree of difficulty during defecation will be recorded in stool diaries with scores ranging from 0 (no difficult) to 3 (too difficult that need assistant methods). Change of straining level from baseline to the last 2 weeks of treatment period will be compared.

##### Patient Assessment of Constipation Symptoms (PAC-SYM)

The PAC-SYM is commonly used to value the presence and severity of constipation on 3 subscales including abdominal symptoms, stool symptoms, and rectal symptoms [26]. A scoring range of 0 to 4 is derived for each item. The PAC-SYM will be measured at baseline, week 4, and week 8.

##### Patient Assessment of Constipation Quality of life questionnaire (PAC-QOL)

PAC-QOL is capable to reflect life quality related to constipation on four subscales by scoring 28 items including physical discomfort, psychosocial discomfort, worries and concerns, and satisfaction [27]. In each item, the score ranges from 0 to 4 with lower scores indicating greater impairment or dissatisfaction. PAC-QOL will be assessed at baseline, week 4, and week 8.

##### Brief Psychiatric Rating Scale (BPRS)

BPRS is designed as a convenient tool to evaluate the severity of schizophrenic states [28]. It contains 18 items rated on a 7-point Likert scale, from 1 representing not present to 7 representing extremely severe. The BPRS will be measured at baseline and week 8.

##### Blinding assessment

To test the success rate of blinding, all participants will be requested to guess their groups by choosing one of the 3 options including EA group, SA group, or unclear at week 8.

##### Credibility and expectancy

The credibility and expectancy will be evaluated through the Credibility/Expectancy Questionnaire after the first treatment [29].

##### Use of rescue medicine and other assistant methods

The use of rescue medicine and other assistant methods will be documented in stool diaries. The proportion and frequency of participants using rescue medicine or other assistant methods will be reported and compared between groups.

##### Adverse events

All adverse events will be clearly recorded, managed, and monitored during the study, which will be collected through (1) inquiries by outcome assessors after each treatment and at the time of recycling stool diaries (every 2 weeks during the treatment period and every 4 weeks during the follow-up period); (2) identification from laboratory values as reported by clinicians during hospitalization; and (3) self-report by participants at any time during this study. Possible treatment-related adverse events include local bleeding, hematoma, itching, and dizziness, etc. Serious adverse events (e.g., death, life-threatening condition; severe or permanent disability, prolonged hospitalization) will be reported within 24 h to the principal investigator. Adverse events will be managed by acupuncturists or clinicians at the Beijing Changping Hospital of Integrated Chinese and Western Medicine based on its association to the intervention. An independent data and safety monitor board (DSMB) comprises experts who have an intimate knowledge of constipation, schizophrenia, and methodology is established to surveil the safety.

### Data collecting method

All measurements in this study will be completed by either outcome assessors or caregivers. The stool diary will be maintained by caregivers who will be trained to ask standard questions, identify the stool types based on the Bristol Stool Form Scale, and make the record at bedtime (no bowel movement in a day) or within 5 min after each bowel movement. The diary will be recycled every 2 weeks during the treatment period, and every 4 weeks during the follow-up period. Data will be collected and transferred to the paper case report forms (CRFs). Participants deviating from the study protocol (e.g., discontinuing intervention) will be encouraged to complete the stool diary and the remaining assessments. No biological specimens will be collected in this study.

### Data management

When completing the whole study, double data entry will be conducted by two independent researchers using EpiData, version 3.1 for proofreading. The principal investigator will have full access to the final database of this study. Other investigators are limited to accessing the final data without permission from the principal investigator. The result of the study will be published in a peer-reviewed journal. Participants’ information will remain anonymous including name, age, and telephone number, etc. All data related to the trial will be saved for at least 5 years after publication. The researcher with the approved proposal will be permitted to access the data by contacting the corresponding authors.

### Quality control

To ensure the accuracy, consistency, and completeness of the data, the outcome assessor will be responsible for guiding, reminding, and supervising the record of the stool diary. Data of this study will be monitored primarily by the center leaders. The study designers from the Beijing University of Chinese Medicine will audit the study semi-annually to ensure the overall quality and the completeness of data.

### Sample size

Referring to a previous study [30], the change from baseline in mean weekly CSBMs during week 1 to week 8 is about 1.8 in the EA group and 0.9 in the SA group with a standard deviation of 1.6. A calculated sample size of 50 participants in each group is estimated based on a significant level of 0.05 and a statistical power of 0.8. When considering a dropout rate of 10%, 56 participants are needed in each group, 112 participants in total.

### Statistical analysis

A professional statistician who is blinded to the allocation will analyze data using IBM SPSS21.0. Continuous variables will be presented as mean (standard deviation) or the median (interquartile range) based on data distribution. Categorical variables will be described by frequencies and percentages. Statistical analysis will follow the intention-to-treat principle predominately for participants who have been randomized. Missing data for the primary outcome will be imputed using the multiple imputation method. The alternative hypothesis is that there is a significant difference between EA and SA groups in the change of mean weekly CSBMs over an 8-week treatment period from baseline.

For the primary outcome, analysis of covariance (ANCOVA) model will be used with treatment and corresponding baseline value as covariates. Repeated measures ANCOVA with the same covariates will be implemented for change from the baseline of mean weekly CSBMs during the follow-up period, and change from baseline of mean weekly SBMs. An independent *t* test or Wilcoxon rank-sum test will be implemented for scores on BSFS, straining level, BPRS, credibility and expectancy, and mean weekly frequency of rescue medicine and other assistant methods used. The difference in overall CSBM response rate, blinding, adverse events, and proportion of participants using rescue medicine or other assistant methods will be compared using the Pearson *χ*^2^ test or Fisher’s exact test. Repeated measures ANOVA or Kruskal-Wallis *H* test will be implemented for scores on PAC-SYM and PAC-QOL. All significance levels will be set at 0.05 (two-sided) with confidence intervals reported.

As sensitive analyses, a per-protocol analysis will exclude data from participants who complete less than 16 sessions (80% of total treatment sessions) or use other medicines to treat constipation for more than 3 days per week on average. No additional analyses will be performed.

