#### Secondary outcomes

##### Change from baseline of mean weekly CSBMs during the follow-up period

Similar to the primary outcome, change from baseline of mean weekly CSBMs in the rest of three 4-week periods (from weeks 9 to 12, weeks 13 to 16, and weeks 17 to 20) will be calculated and compared between groups. The data will be used to verify whether there is a sustained effect by showing the extent.

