##### Change from baseline of mean weekly SBMs

Change from baseline of mean weekly SBMs during the 8-week treatment period and 12-week follow-up period will be assessed.

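### Follow-up CSBMs and SBMs: repeated measures ANCOVA with no stated handling of missing periods and no treatment-by-period contrast secures neither intention-to-treat nor a view of how long the effect lasts

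*Protocol article*

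**What the plan says.** All analysis statements here are in the protocol article, section Statistical analysis.

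- Method for follow-up CSBMs: "Repeated measures ANCOVA with the same covariates will be implemented for change from the baseline of mean weekly CSBMs during the follow-up period". The sentence continues "and change from baseline of mean weekly SBMs", so SBMs get the same model.
- Covariates: these are carried over from the primary analysis, where the "analysis of covariance (ANCOVA) model will be used with treatment and corresponding baseline value as covariates". No period term, treatment-by-period term or per-period contrast is named.
- Population: "Statistical analysis will follow the intention-to-treat principle predominately for participants who have been randomized".
- Missing data: "Missing data for the primary outcome will be imputed using the multiple imputation method". Nothing is said for other continuous outcomes, and analyses beyond the per-protocol sensitivity analysis are ruled out.
- Software: the statistician "will analyze data using IBM SPSS21.0". The procedure is not named.

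The outcome sections set the aims. Follow-up CSBMs are defined over weeks 9 to 12, 13 to 16 and 17 to 20 and compared between groups, with this purpose: "The data will be used to verify whether there is a sustained effect by showing the extent". For SBMs: "Change from baseline of mean weekly SBMs during the 8-week treatment period and 12-week follow-up period will be assessed". How the SBM weeks are divided into periods is not stated. Under Data collecting method, participants who stop the intervention are encouraged to keep up the diary.

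**The concern.** Two things do not fit together.

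First, the plan promises an analysis of everyone randomized, but it gives these outcomes no way to keep a participant whose diary is incomplete. The usual repeated measures procedure needs every period for every participant. One missing 4-week block then removes the periods that were recorded, including the partial diaries the trial asks discontinuing participants to provide. If those who leave differ in response from those who stay, the comparison is biased as well as less precise.

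Second, the follow-up data are meant to show whether, and to what extent, the effect is sustained. With only treatment and baseline named, the reported effect would naturally be the group main effect, which is an average over periods. An average cannot separate an effect that persists to week 20 from one that has gone by then. For SBMs the average could also span treatment and follow-up weeks, so a benefit confined to treatment could be reported as an overall benefit.

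**Working it through.** **1. The plan's own figure.** Inputs from Sample size: changes of 1.8 and 0.9 (difference 0.9), SD 1.6, alpha 0.05, power 0.80, dropout 10%. Two-sided testing is from Statistical analysis.

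n per group = 2 × (1.960 + 0.842)² × 1.6² / 0.9² = 49.6, rounded up to 50. Then 50 / 0.9 = 55.6, rounded up to 56, or 112 in total. The stated sizes reproduce. They concern the primary outcome and are not in dispute.

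**2. Loss from the stated dropout.** 0.10 × 112 = 11.2 participants, leaving 56 × 0.90 = 50.4 per arm with complete data if dropout is the only source of missing periods.

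**3. Loss from scattered missing periods (assumed).** If each period is missing independently with probability p, the fraction complete over k periods is (1 − p)^k. The article gives no p, so a range is shown. Three periods is the article's CSBM structure. Five 4-week blocks for SBMs (two on treatment, three in follow-up) is an assumption.

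| p (assumed) | k = 3: complete | per arm of 56 | k = 5: complete | per arm of 56 |
|---|---|---|---|---|
| 2% | 94.1% | 52.7 | 90.4% | 50.6 |
| 5% | 85.7% | 48.0 | 77.4% | 43.3 |
| 10% | 72.9% | 40.8 | 59.0% | 33.1 |

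At 5% the excluded share is 1 − 0.95³ = 14.3% for three periods and 1 − 0.95⁵ = 22.6% for five.

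**4. Bias under complete-case analysis (assumed scenario).** A simulation of 4,000 trials used 56 per arm, three periods, SD 1.6, between-period correlation 0.6 and true period effects of 0.9, 0.6 and 0.3 (mean 0.60). About 15% of participants left after the first period, with lower first-period values making leaving more likely.

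| Dropout depends on first-period response | Complete-case estimate | Likelihood-type estimate using all observed periods |
|---|---|---|
| in both arms alike | 0.51 | 0.60 |
| in the sham arm only | 0.36 | 0.60 |

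**5. What the average hides.** Period effects of 1.2, 0.6 and 0.0 average (1.2 + 0.6 + 0.0) / 3 = 0.60. Effects of 0.9, 0.6 and 0.3 also average 0.60. The first has vanished by weeks 17 to 20 and the second has not, yet the group main effect is the same.

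**The case against.** The strongest reply is that the article names a family of methods, not a procedure. It never says general linear model or listwise deletion, and the same software fits mixed models that keep incomplete cases. A condensed article may leave such details to a fuller document. This stands to the extent that exclusion of incomplete participants is inferred from the method's name. It does not remove the point. The article does fix a method, mentions no mixed model, places repeated measures ANOVA, t tests and rank tests beside it, ties imputation to one outcome and closes the list of analyses. The ordinary reading of that set is the complete-case procedure.

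A reader might infer that the plan does not test a sustained effect at all. The documents do not support that. The follow-up CSBM outcome contains no treatment weeks, so even its averaged group effect tests a post-treatment difference. The outcome section says the three periods are compared between groups, and repeated measures output normally includes a group-by-time test. That test, however, asks whether the effect changes over periods, not whether one remains in the last.

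A reader might also infer that intention-to-treat is breached outright. It is not, if diaries are complete. Inpatient recruitment, trained caregivers, supervision of the diary and continued recording after discontinuation all work toward that.

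Finally, the 10% dropout is already budgeted: about 50 per arm remain, the number the calculation requires. That answers the concern about precision for this loss alone. It does not answer selection, or the discarding of partial diaries.

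**Conclusion.** The point holds in a limited form. As written, follow-up CSBMs and SBMs have no stated handling of missing periods that would carry out the intention-to-treat principle, and no contrast that shows duration. In the method's usual form, the analysis rests on completers as soon as a period is missing. The documents support one size: the planned 10% dropout, about 11 of 112. The 14% and 23% figures rest on an assumed 5% independent loss per block and, for SBMs, on five blocks the article does not state. The biased estimates of 0.36 to 0.51 against 0.60 rest on an assumed dropout mechanism, and they illustrate direction and possible scale rather than forecast it.

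That treatment and follow-up SBM weeks enter one averaged effect is a possibility the wording leaves open, not something it states. These are secondary outcomes, so the primary analysis and the sample size are unaffected. The change is still worth making, because a durability claim is an explicit aim of the trial.

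**What to change.** Replace repeated measures ANCOVA for these two outcomes with a linear mixed model (SPSS MIXED) that uses all available periods from all randomized participants, with treatment, period, treatment-by-period and baseline value as fixed effects and a stated covariance structure for the repeated periods.

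- **Follow-up CSBMs:** report the adjusted between-group difference with confidence interval for each of weeks 9 to 12, 13 to 16 and 17 to 20.
- **SBMs:** state the periods, and report the treatment-period and follow-up contrasts separately.
- **Early leavers:** a participant who leaves before week 9 has no follow-up period to contribute. Either include the treatment-period values as earlier periods in the CSBM model or extend the multiple imputation to these outcomes, and say which.

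If a mixed model was intended all along, a sentence or two naming it and the contrasts settles the matter. The cost is wording only: same data and same software. The Trial status section reports that recruitment has not begun, so the change can be made before any data exist.

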##### Bristol Stool Form Scale

The BSFS describes 7 stool types from hard lumps of stool to watery stool with aid images. Change of mean weekly scores on BSFS from baseline to the last 2 weeks of the treatment period will be compared between groups to detect a possible difference in stool consistency.

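### BSFS, straining level and BPRS are tested without a baseline covariate although their baselines are collected: a minor, nearly free gain in precision on secondary outcomes

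*Protocol article*

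**What the plan says.** In the Protocol article, the Statistical analysis section assigns an independent t test or "Wilcoxon rank-sum test will be implemented for scores on BSFS, straining level, BPRS, credibility and expectancy", and then adds the frequency of rescue medicine and other assistant methods to the same list. It names no covariate for any of these.

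The same paragraph treats other outcomes differently. For the primary outcome, an "analysis of covariance (ANCOVA) model will be used with treatment and corresponding baseline value as covariates". For two secondary outcomes, "Repeated measures ANCOVA with the same covariates will be implemented for change from the baseline of mean weekly CSBMs during the follow-up period", and likewise for change in SBMs. The section closes by ruling out further analyses beyond those listed.

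Baselines exist for all three scales at issue:

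- Bristol Stool Form Scale: "Change of mean weekly scores on BSFS from baseline to the last 2 weeks of the treatment period will be compared between groups".
- Straining level: "Change of straining level from baseline to the last 2 weeks of treatment period will be compared".
- BPRS: "The BPRS will be measured at baseline and week 8". Neither the BPRS section nor the Statistical analysis section says whether the change or the week-8 score is compared.

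Credibility and expectancy, listed with them, is measured only after the first treatment and has no baseline.

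**The concern.** When a pre-treatment value of the same measure is available, a test that does not use it as a covariate is usually less precise than ANCOVA. The plan accepts this for CSBMs and SBMs but departs from it, without giving a reason, for BSFS and straining, which come from the same stool diary, and for BPRS. At stake is the width of the confidence intervals on stool form, straining and psychiatric state, and the power of those comparisons. For BPRS there is a second point: a test of change and a test of week-8 scores can give different answers in the same data, and the article leaves that choice open.

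**Working it through.** **The plan's own figure.** The Sample size section gives a change that "is about 1.8 in the EA group and 0.9 in the SA group with a standard deviation of 1.6", with significance level 0.05 and power 0.80. The difference is 1.8 − 0.9 = 0.9. Then n = 2 × (1.6 × (1.960 + 0.842) / 0.9)² = 49.6, so 50 per arm. With 10% dropout, 50 / 0.9 = 55.6, so 56 per arm and 112 in total. This reproduces. It concerns CSBMs only; the article gives no SD, effect or power for BSFS, straining or BPRS.

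**Variance per participant.** Let s0 and s1 be the SDs of the score at baseline and at the end, and r their correlation within arm.

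- Final score: s1²
- Change score: s0² + s1² − 2·r·s0·s1
- ANCOVA: s1²(1 − r²)

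Change minus ANCOVA is (s0 − r·s1)², which is never negative. Final minus ANCOVA is r²·s1², also never negative. The direction therefore does not depend on the value of r or on equal SDs.

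With s0 = s1 (assumed), the three variances are 1, 2(1 − r) and 1 − r² in units of s1². So ANCOVA/change = (1 + r)/2 and ANCOVA/final = 1 − r². The reduction in CI width is 1 minus the square root of the ratio.

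| Assumed r | ANCOVA/change | CI narrower by | ANCOVA/final | CI narrower by |
|---|---|---|---|---|
| 0.3 | 0.65 | 19% | 0.91 | 5% |
| 0.5 | 0.75 | 13% | 0.75 | 13% |
| 0.7 | 0.85 | 8% | 0.51 | 29% |
| 0.8 | 0.90 | 5% | 0.36 | 40% |

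The change columns apply to BSFS and straining. The final-score columns can apply only to BPRS, and only if the week-8 score is what is tested.

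**Power.** Inputs: 50 evaluable per arm (Sample size section), two-sided 0.05 (Statistical analysis section), and an assumed effect of 0.5 SD of the raw score. Noncentral t, with one degree of freedom fewer for ANCOVA:

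| Assumed r | t test on change | ANCOVA |
|---|---|---|
| 0.3 | 55% | 74% |
| 0.5 | 70% | 82% |
| 0.7 | 89% | 93% |
| 0.8 | 97.5% | 98.5% |

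**Cost of the covariate.** At N = 100, estimating one slope inflates variance by about 1 + 1/(100 − 4), or 1%. The gain exceeds this unless r is about 0.98 or more (against change) or about 0.1 or less (against final scores).

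**BPRS, change or final.** Write Y for week 8, B for baseline and T for treatment. If Y − B = a + tT + bB, then Y = a + tT + (b + 1)B. The treatment effect t and its CI are identical, so with baseline in the model the open choice no longer matters.

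**The case against.** The strongest reply is that nothing planned here is wrong. Under randomisation the t test and the Wilcoxon test keep their type I error, the outcomes are secondary, and no stated figure changes. That stands, and it limits the point to a minor improvement. Nor can the point be left to an unseen analysis plan: the article names the test and excludes further analyses.

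BSFS and straining already use baseline by subtraction, so calling them unadjusted is right only in the sense of having no covariate. That stands too. A reader might apply the larger final-score savings to all three scales; the definitions of BSFS and straining do not allow it.

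The size depends on a correlation that the article does not give. Quoting only the step from 70% to 82% would suggest a typical gain, but it belongs to one assumed r and one assumed effect. At r = 0.8 the gain is one percentage point.

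Two further inferences are tempting and unsupported. One is that unrestricted randomisation leaves these outcomes exposed to chance imbalance. The Randomization section says 1:1 from a computer-generated sequence and does not say whether it is simple, blocked or stratified. The other is that BPRS precision matters specially because BPRS is the evidence that EA does not worsen mental state. The article presents BPRS as a severity measure, sets no non-worsening hypothesis or margin, and assigns safety to adverse-event collection and a monitoring board.

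Finally, straining is a short ordinal score (0–4 under Primary outcome, 0–3 under Straining level, which need reconciling) and BSFS has seven ordered types. A rank-based option is reasonable for such data and should be kept.

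**Conclusion.** The point holds as a minor, nearly free improvement to three secondary analyses. It is a loss of efficiency, not of validity, and the primary analysis is not touched. For BSFS and straining the CI would be about 5% to 19% narrower over r from 0.8 down to 0.3. For BPRS the same range applies if change is tested, and about 5% to 40% over r from 0.3 up to 0.8 if the week-8 score is tested. These sizes rest on assumed correlations and equal SDs at the two times; the power figures rest also on an assumed 0.5 SD effect with 50 per arm. The direction of the gain rests on none of these, apart from the roughly 1% cost of the covariate.

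**What to change.** In the Statistical analysis section, move BSFS, straining level and BPRS out of the t test/Wilcoxon sentence. Analyse each by ANCOVA with treatment and the corresponding baseline value, as for the primary outcome, and report the adjusted difference with its 95% CI. State that a rank-based ANCOVA will be used where the distribution is clearly non-normal. Keep the t or Wilcoxon test for credibility and expectancy, which has no baseline, and leave the rescue-medicine frequency analysis as stated.

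The cost is one line of wording and one degree of freedom per outcome. No new data are needed and the sample size of 112 does not change. The Trial status section reports no recruitment at the time of the article, so the wording could be settled before any data existed.

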**Methods:**

This is a single-centric, parallel-group, randomized controlled trial with blinded participants, outcome assessor, and statistician. One hundred twelve participants will be randomly assigned into the EA group or sham acupuncture (SA) group in a 1:1 ratio. The study will last for 22 weeks for each participant, including a 2-week baseline assessment period, an 8-week treatment period, and a follow-up for 12 weeks. The primary outcome is the change of mean weekly complete spontaneous bowel movements (CSBMs) during weeks 1 to 8 from baseline. Secondary outcomes include the change from baseline of mean weekly CSBMs during the follow-up period, mean weekly spontaneous bowel movements (SBMs), overall CSBM response rate, scores on Bristol Stool Form Scale (BSFS), straining level, Patient Assessment of Constipation Symptoms (PAC-SYM), Patient Assessment of Constipation Quality of life questionnaire (PAC-QOL), and Brief Psychiatric Rating Scale (BPRS). Adverse events and medicine use will be recorded as well.

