##### Overall CSBM response rate

Participants are thought to be responders when they have ≥3 CSBMs and ≥1 CSBM increasing from baseline for at least 6 weeks of the treatment period [25]. If participants miss recording stool diaries for at least 4 of 7 days in a given week, they will not be considered as responders during that week. Participants who discontinue the study prematurely will be classified as non-responders for the rest of the weeks.

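### The secondary overall CSBM response rate is compared without adjusting for baseline CSBMs; the test is valid, but it forgoes a small amount of precision

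*Protocol article*

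**What the plan says.** The section on the overall CSBM response rate counts a participant as a responder with "≥3 CSBMs and ≥1 CSBM increasing from baseline for at least 6 weeks of the treatment period". The Statistical analysis section assigns this outcome to a two-by-two comparison: "The difference in overall CSBM response rate, blinding, adverse events, and proportion of participants using rescue medicine or other assistant methods will be compared" by Pearson chi-square or Fisher's exact test. No covariate is named.

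The same section treats the related diary outcomes differently. For the primary outcome, an "analysis of covariance (ANCOVA) model will be used with treatment and corresponding baseline value as covariates". Follow-up CSBMs and SBM changes get a repeated measures ANCOVA with the same covariates. The section closes with "No additional analyses will be performed", so no baseline-adjusted responder analysis is planned in this document.

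The baseline count needs no new data. The Abstract describes each participant's time in the study as "including a 2-week baseline assessment period, an 8-week treatment period, and a follow-up for 12 weeks", and the stool diary runs throughout.

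**The concern.** Response and the primary outcome come from the same diary, the same eight weeks and the same baseline. A participant who enters with 2 CSBMs a week needs a smaller rise to reach 3 than one who enters with none, so baseline may predict response. The plan uses that information for the mean change and ignores it for the responder version.

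Two things are at stake, both modest. Some precision is lost on an outcome that dichotomising has already made less informative. Also, the Randomization section mentions no stratification by baseline CSBM. A chance difference between arms would be corrected in the primary analysis but left in the responder comparison.

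**Working it through.** **1. The plan's own figure.** The Sample size section says the change "is about 1.8 in the EA group and 0.9 in the SA group with a standard deviation of 1.6", with alpha 0.05 (two-sided under Statistical analysis) and power 0.80.

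n per arm = 2 × (1.960 + 0.842)² × 1.6² / 0.9² = 15.70 × 2.56 / 0.81 = 49.6, so 50 (a t-based calculation gives 50.6). Allowing for 10% dropout, 50 / 0.90 = 55.6, so 56 per arm and 112 in total. The figure reproduces. It concerns the primary outcome only; no power is stated for response.

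**2. How baseline enters the rule.** A week qualifies if its count is at least max(3, baseline + 1). For a baseline of 2 or less, baseline + 1 is at most 3, so the second condition adds nothing and the rise needed is 3 − baseline. Taking baseline as a two-week mean, the highest value below 3 is 2.5; such a participant needs 3.5, that is, 4 CSBMs. If each baseline week must be below 3, the highest baseline is 2 and the second condition never bites. Its place in the definition therefore does not by itself make baseline strongly prognostic. The entry limit of under 3 and the two-week measurement also restrict its range and add noise.

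**3. Analytic size.** If r is the within-arm correlation of baseline with response, adjustment multiplies the effective sample size by about 1/(1 − r²). Responder rates and r are assumptions. With 56 per arm:

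| r | Effective n | Power, 20% vs 40% | Power, 10% vs 30% |
|---|---|---|---|
| 0 (unadjusted) | 1.00 | 0.640 | 0.761 |
| 0.1 | 1.01 | 0.644 | 0.765 |
| 0.2 | 1.04 | 0.658 | 0.778 |
| 0.3 | 1.10 | 0.682 | 0.800 |
| 0.4 | 1.19 | 0.717 | 0.831 |
| 0.5 | 1.33 | 0.766 | 0.871 |

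**4. What r is plausible.** The responder rule was simulated with 56 per arm, mean changes of 0.9 and 1.8 and an SD of change of 1.6 (before weekly counts were rounded and floored at zero). Assumed, not in the protocol: baseline mean parameter 0.9, baseline SD parameter 0.6, 0.9 or 1.5 before restriction to 0 to under 3, slope of post-treatment on baseline 0.3, 0.6 or 1.0, and within-person weekly SD 1.2. There were 1,500 runs per setting. Response was 23 to 28% in SA and 43 to 47% in EA.

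| Slope | r | Relative efficiency | Chi-square power | Adjusted power | Change (points) |
|---|---|---|---|---|---|
| 0.3 | 0.00 to 0.06 | 0.99 to 1.00 | 0.628 to 0.650 | 0.635 to 0.644 | −0.6 to +1.4 |
| 0.6 | 0.11 to 0.13 | 1.01 | 0.607 to 0.618 | 0.622 to 0.635 | +0.8 to +1.8 |
| 1.0 | 0.23 to 0.24 | 1.03 to 1.07 | 0.556 to 0.581 | 0.585 to 0.612 | +1.8 to +3.1 |

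Each power estimate has a Monte Carlo standard error of about √(0.6 × 0.4 / 1500) = 1.3 points, so the small negative values are compatible with zero. A separate gamma-Poisson simulation with the same mean changes gave lower response (24 to 35% EA, 11 to 18% SA) and a gain of 1 to 2 points: 43 to 51% by chi-square, 44 to 52% adjusted.

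**5. Validity.** With no treatment effect (2,000 runs), the chi-square test rejected in 5.2% of trials, Fisher in 2.9% and the adjusted likelihood-ratio test in 5.6%.

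**6. Chance imbalance.** With 56 per arm, the baseline difference has a standard error of √(2/56) = 0.19 baseline SDs. Take r = 0.244 and response of 26.3% and 44.8% (slope 1.0, SD parameter 0.9). The within-arm SD of response is √[(0.194 + 0.247)/2] = 0.47. An imbalance of one standard error then moves the risk difference by 0.244 × 0.47 × 0.19 = 0.022. The standard error of that difference is √[(0.194 + 0.247)/56] = 0.089.

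**The case against.** The strongest reply is that nothing here is wrong. A Pearson or Fisher test of a secondary binary outcome in a randomised trial is standard and valid, the trial is not sized on it, and adjusting one outcome but not another is no contradiction. All of that stands, and it limits the point to an optional improvement.

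Part of even the small simulated gain may not come from baseline, because both simulations compare a Pearson test with a likelihood-ratio test. With no covariate at all, exact enumeration at 24% vs 11% gives power of 45.1% by Pearson and 46.3% by likelihood ratio. The latter's null size is 5.7 to 5.9% at rates of 11 to 15%, against 5.0% for Pearson. At 35% vs 18% the switch makes no difference. This also stands, as a reason to read the gain as small.

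Four stronger readings are tempting, and the protocol does not support them:
- **The planned comparison is biased or invalid.** Randomisation rules this out, and the null simulation agrees.
- **Adjustment could add about 10 power points.** A rise from 71% to 81% appears only when response of 35% vs 15% and a latent correlation of 0.6 are assumed. That implies an observed correlation of about 0.39 to 0.47, against 0.00 to 0.24 when the responder rule is simulated. None of these figures is in the protocol.
- **No confidence interval is possible.** An interval for a difference in proportions can accompany either test. The protocol promises intervals, and the formula is detail for an analysis plan.
- **Any disagreement with the primary result would reflect baseline imbalance.** A rule of six weeks in eight and a mean change are different outcomes and can disagree even when both are adjusted.

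What survives is that the document names an unadjusted test and closes the list of analyses, although a usable covariate is at hand.

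**Conclusion.** The point holds as a minor one. The planned responder test is valid but forgoes some precision and leaves chance baseline imbalance in the estimate. With the protocol's changes and SD and the assumed baseline distributions, slopes and weekly variation, the gain from adjusting is about 0 to 3 power points, or 0 to 7% in efficiency. A gain of 10% or more in effective sample size needs a within-arm correlation of about 0.3 or higher, and the protocol gives nothing to settle that. For scale, Fisher's test lost 6.5 to 8.7 points against the uncorrected chi-square in the same simulation, more than the lack of adjustment did. The primary analysis and the sample size are unaffected. Adjustment should not be described as always free, since at the low end it gains nothing.

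**What to change.** Prespecify a logistic regression of overall CSBM response on treatment and baseline mean weekly CSBMs, the covariate already used in the primary ANCOVA. Report the baseline-standardised risk difference with its 95% CI. Keep the Pearson or Fisher result as the unadjusted supporting analysis.

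State one rule for sparse responders in advance, so that the choice of model does not depend on the data. Examples are penalised logistic regression, or a stated minimum number of responders below which only the unadjusted test is reported.

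The cost is a sentence or two in the analysis section and one extra model, with slight instability if responders are few. No extra participants or data are needed. The Trial status section reports no recruitment so far, so on that status the change can still be made before any data exist.
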